## 7. SELECTION CRITERIA

### 7.1 Inclusion Criteria

#### 7.1.1 TME-participants

TME-participants must meet all the following criteria to be eligible to enroll in the study:

- Healthy male
- Age above 18 yrs and below 65 yrs
- Signed informed consent
- Participants submitted to unilateral, primary, impacted, uncomplicated mandibular third molar extraction 4 weeks ( $\pm$  3 days) prior to examination Day 1.
- Standardized surgical procedure.
- Urin-sample *without* traces of opioids (morphine, methadon, buprenorphine, codeine, tramadol, ketobemidone, oxycodone, hydromorphone, dextromethorphan)
- ASA I-II
- Body mass index (BMI):  $18 < \text{BMI} < 30 \text{ kg/m}^2$

#### 7.1.2 BI-participants

BI-participants must meet all the following criteria to be eligible to enroll in the study Day 0:

- Healthy male
- Age above 18 yrs and below 35 yrs
- Signed informed consent
- Urin-sample *without* traces of opioids (morphine, methadon, buprenorphine, codeine, tramadol, ketobemidone, oxycodone, hydromorphone, dextromethorphan)
- ASA I

- Body mass index (BMI):  $18 < \text{BMI} < 30 \text{ kg/m}^2$

In addition, BI-participants must meet the following criteria to be eligible to further enroll in the study Day 1-4:

- Secondary hyperalgesia areasC 1 hr after a burn injury ( $47^\circ\text{C}$ ,  $2.5 \times 5.0 \text{ cm}^2$ , 7") either  $\geq 37 \text{ cm}^2$  (high-sensitizers) or  $\leq 22 \text{ cm}^2$  (low-sensitizers). The selection into high-sensitizers and low-sensitizers is made during a separate test day (Day 0).

## 7.2 Exclusion criteria

### 7.2.1 TME-participants

TME-participants, who meet one or more of the following criteria, are not suitable for inclusion in this study:

- Participants, who do not speak or understand Danish
- Participants, who cannot cooperate with the investigation
- Participants, who have had previous surgery in the mandibular region
- Participants with pain at rest  $> 3$  (NRS [0: no pain; 10: worst perceivable pain])
- Activity-related pain in the surgical field  $> 5$  (NRS)
- Allergic reaction against morphine or other opioids (including naloxone),
- Abuse of alcohol or drugs – according to investigator's evaluation
- Use of psychotropic drugs (exception of SSRI)
- Neurologic or psychiatric disease
- Chronic pain condition
- Regular use of analgesic drugs
- Skin lesions or tattoos in the assessment areas
- Nerve lesions in the assessment sites (e.g., after trauma, dental surgery)
- Use of prescription drugs one week before the trial
- Use of over-the-counter (OTC) drugs 48 hours before the trial

### 7.2.2 BI-participants

BI-participants, who meet one or more of the following criteria, are not suitable for inclusion in this study:

- Participants, who do not speak or understand Danish
- Participants, who cannot cooperate with the investigation
- Allergic reaction against morphine or other opioids (including naloxone)
- Abuse of alcohol or drugs – according to investigator's evaluation
- Use of psychotropic drugs (exception of SSRI)
- Neurologic or psychiatric disease
- Signs of neuropathy in the examination region
- Previous severe trauma to the lower legs with sequelae
- Scarring or tattoos in the examination areas
- Chronic pain condition
- Regular use of analgesic drugs
- Use of prescription drugs one week before the trial

---

C Secondary hyperalgesia areas are calculated after subtracting the primary hyperalgesia area ( $12.5 \text{ cm}^2$ ). Data from: Ringsted TK, Enghuus C, Petersen MA, [name] (2015) Demarcation of secondary hyperalgesia zones: Punctate stimulation pressure matters. J Neurosci Methods 256: 74-81.

- Use of over-the-counter (OTC) drugs 48 hours before the trial
- Does not develop measurable secondary hyperalgesia areas after BI

## 8. PRACTICAL CONSIDERATIONS

### 8.1 Economical issues

[name] has in collaboration with the research partners ([name], [name], [name], [name], and [name]) taken the initiative to this study. Expenses of the study include costs regarding: reimbursement to the participants, and, costs of the study drug, submission fees to the Danish Medicines Agency, salary to research nurse and miscellaneous (e.g. statistical assistance, computer-hardware and computer-software). All staff members involved in the study are employed at the Multidisciplinary Pain Center 7612, Neuroscience Center, Rigshospitalet. Incurred costs will be paid from the research fund of [name], subjected to audit from the hospital-administration. In a consortium agreement with the University of Kentucky Research Foundation we have September 2015 received a research award from the National Institute of Health (NIH), U.S.A. for research entitled, “Long-term activation of spinal opioid analgesia after inflammation”. Major part of the cost will be paid from this resource.. A budget specification is given in paragraph 15.2 (page 33).

Neither the sponsor/principal investigator, nor any of the research-partners have any financial interest in the study.

### 8.2 Participant inclusion and withdrawal from the study

- A participant, who has completed the trial, is a participant, who has followed the complete treatment and assessment plan of the study in the required 2 hours of both study days.
- A participant, who has not completed the trial, is a participant, who was included in the trial (i.e. has signed the informed consent), but did not complete the trial, regardless of having received the study drug or not.
- If a participant has not completed the trial, the procedures regarding this participant must be specified – this is also valid for drop-outs – and also what data is collected from these subjects.

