possibility that participants will experience short lasting pain or unpleasantness from the surgical area. This may be uncomfortable for the participant, but is essential to answer the questions asked in this study. If requested by the participant, the rapid-onset, analgesic, rescue-opioid, alfentanil, will be administered, which in less than one min completely will antagonize the effects of naloxone. Alfentanil is a well-known drug used in anesthesia for immediate relief of acute pain. Alfentanil is initially given 7-15 mikrog/kg (1-2 ml/70 kg) and is administered in a titrated fashion until the desired analgesic effect is achieved. Common dose-dependent side effects are nausea, vomiting and sedation (> 10%). During the naloxone-infusion the participant's resting pain is monitored. The naloxone-infusion is immediately stopped if the participant experiences resting pain levels  $\geq 5$  (NRS 0-10).

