## **6. STUDY DESIGN**

### **6.1 TME-participants**

|                |                                                                                                  |
|----------------|--------------------------------------------------------------------------------------------------|
| Study type:    | Randomized, placebo-controlled, double-blind crossover                                           |
| Randomization: | Computer generated randomization list, closed envelopes                                          |
| Phase:         | Phase 2                                                                                          |
| Blinding:      | Double-blind, crossover                                                                          |
| Subjects:      | Participants with unilateral, primary, uncomplicated, impacted mandibular third molar extraction |
| Number:        | 14 evaluable subjects (maximum included number: 18)                                              |

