#### 12.4 Procedures in case of emergency

The investigator will ensure that there are planned procedures and the necessary expertise to deal with an emergency situation that may arise during the study. The randomization code (and thus the blinding procedure) should only be broken, if it is necessary to know which drug has been administered to the participant. Individual drug-packages include a sealed, non-transparent envelope containing the randomization sequence code for each participant (paragraph 10.2.1, page 26). This envelope is immediately broken by the investigator should an emergency arise that require un-blinding of the drug. If the code envelope is opened, the date and justification must be registered. The envelope must then be signed by the investigator and the participant will be excluded from the study.

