### 13. STATISTICAL ANALYSES

#### 13.1 Sample size calculations

##### 13.1.1 TME-participants

Sample size calculations are based on following assumptions and estimations (abbreviations: BL = baseline; NX = naloxone; PL = placebo; TCI = during target-controlled-infusion):

1. a primary outcome based on a summed measure (SM) of resting pain (RP), masticatory pain (MP; (movement-related) and pressure-evoked pain (PM; pressure algometry [100 kPa]).  $NRS_{SM} = NRS_{RP} + NRS_{MP} + NRS_{PM}$ .
2. the summed pain intensities (SPIs) are calculated as: (BL-SPINX) and (TCI-SPINX), and, (BL-SPIPL) and (TCI-SPIPL), where (TCI-SPI) indicates SM-value at highest obtainable TCI-step (Fig. 2).
3. the summed pain intensity differences (SPIDs) are the differences: **SPIDNX** = (TCI-SPINX) – (BL-SPINX) and **SPIDPL** = (TCI-SPIPL) - (BL-SPIPL)

4. the mean [SD] BL-pain intensities are estimated to be: resting pain 1 [1] NRS-units; movement related pain 2 [2] NRS-units; pressure evoked pain 4 [2] NRS-units.
5. the mean [SD] summed BL-pain intensity (BL-SPI) is estimated to be 7 [4.1] NRS-units (Table 2).
6. the minimal relevant SPID-difference, calculated as  $\Delta SPID = SPID_{NX} - SPID_{PL}$  is estimated to be 5 (NX-group: RP = 4; MP = 5; PM = 7 [total 16]/PL-group: RP = 2; MP = 4; PM = 5 [total 11]) corresponding to a  $\Delta SPID\% = 45\%$ .
7. the design is a placebo-controlled, randomized, double-blind, crossover study
8. the significance level  $\alpha$  is set to 0.01 and the power is set to  $= 0.90$  ( $\beta = 0.10$ )

The total number of individuals estimated to be included in the study is calculatedE to be 14 (effect size 1.2). Using the range of variances in Table 2, it can be calculated that the number of individuals ranges from 9 to 19, with effect sizes of 1.7 to 1.0, respectively.

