In order to allow for drop-outs the total number of individuals is set to 18. Due to the frail nature of the sample size estimates, an interim-analysis of the primary outcome, performed by an independent statistician, is made after per-protocol inclusion of 14 individuals. If the null hypothesis (no statistical difference between the placebo and the naloxone groups) is rejected, the study is deemed completed. If the new sample size estimates indicate that more than 16 additional individuals (total number of individuals > 30) are required, the study is prematurely discontinued. If less than 16 additional individuals (total number of individuals  $\leq 30$ ) the study continues and is discontinued after the stipulated number has been reached.

| V(X1) | V(X2) | V(X3) | COV(X1,X2) | COV(X1,X3) | COV(X2,X3) | V(SUM) | SD(SUM) | CORR(X1,X2) | CORR(X1,X3) | CORR(X2,X3) |
|-------|-------|-------|------------|------------|------------|--------|---------|-------------|-------------|-------------|
| 1     | 4     | 4     | 0          | 0          | 0          | 9      | 3.00    | 0           | 0           | 0           |
| 1     | 4     | 4     | 0.1        | 0.1        | 0.2        | 9.8    | 3.13    | 0.05        | 0.05        | 0.05        |
| 1     | 4     | 4     | 0.2        | 0.2        | 0.4        | 10.6   | 3.26    | 0.1         | 0.1         | 0.1         |
| 1     | 4     | 4     | 0.3        | 0.3        | 0.6        | 11.4   | 3.38    | 0.15        | 0.15        | 0.15        |
| 1     | 4     | 4     | 0.4        | 0.4        | 0.8        | 12.2   | 3.49    | 0.2         | 0.2         | 0.2         |
| 1     | 4     | 4     | 0.5        | 0.5        | 1          | 13     | 3.61    | 0.25        | 0.25        | 0.25        |
| 1     | 4     | 4     | 0.6        | 0.6        | 1.2        | 13.8   | 3.71    | 0.3         | 0.3         | 0.3         |
| 1     | 4     | 4     | 0.7        | 0.7        | 1.4        | 14.6   | 3.82    | 0.35        | 0.35        | 0.35        |
| 1     | 4     | 4     | 0.8        | 0.8        | 1.6        | 15.4   | 3.92    | 0.4         | 0.4         | 0.4         |
| 1     | 4     | 4     | 0.9        | 0.9        | 1.8        | 16.2   | 4.02    | 0.45        | 0.45        | 0.45        |
| 1     | 4     | 4     | 1          | 1          | 2          | 17     | 4.12    | 0.5         | 0.5         | 0.5         |

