## 13.2 Data processing

### 13.2.1 TME-participants

To test if data is normally distributed, residual plots and the Kolmogorov-Smirnov test will be used (SPSS 20.0, Chicago, IL, USA; MedCalc Software: version 12.07.0.0; Mariakerke, Belgium). In case of non-normal data distribution, primarily a logarithmic transformation is tried or secondarily a Box-Cox transformation will be attempted for normalization of data.

The primary outcome  $\Delta\text{SPID}$  ( $\text{SPID}_{\text{NX}} - \text{SPID}_{\text{PL}}$ ) is analyzed by one-way repeated measures ANOVA ( $\Delta\text{SPID}$ : dependent variable; TCI-steps: independent variable) or a corresponding non-parametric analogue (Friedman test), as appropriate. Paired  $t$ -test or Wilcoxon rank sum test will be used, as appropriate for inter-group comparisons.

A mixed model with random effect for subject and fixed-effects for the factors; *target-controlled-infusion* (step 1/step 2/step 3), *drug* (naloxone/placebo); *secondary hyperalgesia area* (SHA); *pressure pain threshold* (PPT); *HADS-score*; and *PCS-scores*, are used for the primary outcome  $\Delta\text{SPID}$  ( $\text{SPID}_{\text{NX}} - \text{SPID}_{\text{PL}}$ ). Non-significant ( $P > 0.05$ ) factors, beginning with interactions, are excluded until all included factors attain significance. Main-effects and interaction-effects are examined.

The risk of type I error is reduced by setting a significance level of 0.01 ( $\alpha$ ). A power of 0.90 ( $\beta = 0.10$ ) is set in order to reduce the risk of type II errors. For all statistical calculations, in which multiple comparisons are performed, Duncan's new multiple range test or Scheffé's method, as appropriate, will be used. Statistical calculations will be performed with partially un-blinded data, i.e., group A and B. When statistics have been completed, data are unblinded, into naloxone and placebo groups.

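### The TME sections disagree on whether a subject whose infusion is stopped for resting pain stays in the primary analysis, and dropping such subjects would bias ΔSPID towards zero

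*Protocol*

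**What the plan says.** **The stop.** Protocol 4.2.1.1: "The naloxone-infusion is immediately stopped if the participant experiences resting pain levels" of 5 or more on the 0–10 scale. Resting pain is also one of the three ratings summed in the primary outcome (3.1.1 and 13.1.1).

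**The endpoint.** In 13.1.1, TCI-SPI "indicates SM-value at highest obtainable TCI-step". That is one value per study day. SPID is this value minus baseline, and ΔSPID is naloxone SPID minus placebo SPID.

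**The analysis.** In 13.2.1, ΔSPID "is analyzed by one-way repeated measures ANOVA", with infusion step as the independent variable, or by the Friedman test. A paired t-test or Wilcoxon test and a mixed model with a random subject effect are also named.

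**Who counts.** Section 6.1 plans for "14 evaluable subjects (maximum included number: 18"). The interim analysis in 13.1.1 "is made after per-protocol inclusion of 14 individuals". Neither evaluable nor per-protocol is defined. By section 8.2 a completer "is a participant, who has followed the complete treatment and assessment plan of the study in the required 2 hours of both study days". For a non-completer the same section requires that "the procedures regarding this participant must be specified". The protocol then gives no such procedures for the analysis.

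**Code break.** In 12.4, once the code envelope has been opened, "the participant will be excluded from the study".

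**The concern.** The event that interrupts a subject's data is the effect the trial is looking for. The hypothesis is that naloxone brings pain back. A subject in whom resting pain returns strongly enough is stopped, has no later step assessments, and by the wording of 8.2 has not completed. Few subjects should reach the stop on placebo.

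If whoever runs the analysis follows the step-wise ANOVA or Friedman test, or counts only completers towards the 14, the subjects lost are mainly strong naloxone responders. The estimate moves towards no effect. The interim test and the sample size re-estimate, both made at 14 subjects, would rest on the same selected set. If the analyst instead follows the endpoint definition in 13.1.1, most of these subjects stay. In a trial of 14 to 18 people that choice should not be open after the data are in.

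**Working it through.** **1. The plan's own sample size.** Paired t-test with the noncentral t distribution, two-sided α = 0.01 (sidedness is not stated), power 0.90, effect size 5/4.12 = 1.21 (ΔSPID of 5 from 13.1.1; SD from Table 2 at correlation 0.5). This gives N = 14, with power 0.907 at effect size 1.2. Effect sizes 1.7 and 1.0 give 9 and 19. All three agree with 13.1.1, so the sample size is not in question.

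**2. What each section does with a stopped subject.**

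| Section | Rule | Consequence |
|---|---|---|
| 13.1.1, item 2 | one value at the last step obtainable | kept if at least one on-infusion assessment exists (first window 15–25 min) |
| 13.2.1, ANOVA/Friedman | a value at each of three steps | lost under complete-case handling |
| 13.2.1, paired test | one value per day | can be kept |
| 13.2.1, mixed model | partial data usable | can be kept |
| 8.2 | completer definition | non-completer; handling left open |
| 6.1, 13.1.1 | 14 evaluable / per-protocol | undefined |

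A stop before the first window leaves no scheduled on-infusion value under any of these rules.

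**3. How often the stop would occur.** Inputs: planned mean resting pain 4 on naloxone and 2 on placebo (13.1.1, item 6); SD s = 1 (the stated baseline SD, carried over to the infusion) or s = 2 (assumed); normal distribution (assumed).

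P(stop) = 1 − Φ((5 − mean)/s)

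- Naloxone: s = 1, 1 − Φ(1) = 0.159; s = 2, 1 − Φ(0.5) = 0.309.
- Placebo: s = 1, 1 − Φ(3) = 0.001; s = 2, 1 − Φ(1.5) = 0.067.

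Treating the scale as whole numbers (cut at 4.5) gives 31% and 40% on naloxone and 0.6% and 10.6% on placebo, so the figures above are at the low end.

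**4. Shift on one day if stopped subjects are dropped.** With SD 2 for masticatory and pressure pain and correlation 0.5 between components (the Table 2 choice), the fall in mean summed pain is (s + 2·0.5·2)·φ(a)/Φ(a), where a = (5 − mean)/s.

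- Naloxone: s = 1, 3 × 0.2876 = 0.86; s = 2, 4 × 0.5092 = 2.04.
- Placebo: s = 1, 3 × 0.0044 = 0.01; s = 2, 4 × 0.1388 = 0.56.

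**5. Shift in ΔSPID.** Dropping a subject removes both days, so the naloxone-day fall must not be set directly against the planned 5. Let r be the between-day correlation (not given in the protocol), and let baselines cancel between days. Removing anyone stopped on either day:

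- r = 0: loss 0.86 − 0.01 = 0.85 (s = 1); 2.04 − 0.56 = 1.48 (s = 2).
- r = 0.7, s = 1: placebo stops are negligible, so the loss is about (1 − r) × 0.86 = 0.3 × 0.86 = 0.26.
- r = 0.7, s = 2: simulation gives a mean ΔSPID of 4.46, a loss of 0.54.

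The range is therefore about 0.3 to 1.5 of 5 units, always towards zero.

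**6. Power, as an illustration.** A simulation took component differences with means 2, 1, 2 and SDs 1, 2, 2, correlation 0.5, and placebo resting pain held at 2. With 14 treated, about 11.8 remain, mean ΔSPID falls from 5.0 to 4.1 and power from 0.915 to 0.73. With 18 treated, about 15.2 remain and power is 0.88.

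**The case against.** A reader might infer that the protocol removes the strongest naloxone responders from the primary analysis. The documents do not support that.

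- No section links the completer definition in 8.2 to evaluable or per-protocol.
- Section 8.3 lists the participant's wish and protocol violation as grounds for exclusion. A stop under 4.2.1.1 is neither, since it carries out the protocol.
- The endpoint wording in 13.1.1 makes sense only if some subjects were expected not to reach the third step, so the authors seem to have meant to keep them.
- The paired test and the mixed model in 13.2.1 could use partial data.
- Exclusion under 12.4 needs a code break, and a pain stop with rescue does not require one.

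All of this stands. It also stands that analysis sets are often left to the SAP, which is not shown here.

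A reader might also set the naloxone-day shift of 0.86 to 2.04 against the planned 5 and report a loss of 17 to 41%. That overstates the effect, because it ignores that the subject's placebo day is removed with him. The upper end also needs an SD that the protocol does not give. At SD 1, 18 × 0.841 = 15.1 of 18 subjects would remain, more than 14.

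What the objection does not remove is the conflict inside the protocol. The first-named analysis of ΔSPID runs over three steps, while the endpoint is a single value. Section 8.2 requires the handling of non-completers to be specified, and it is not.

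**Conclusion.** The concern holds as a conflict between sections, not as a stated exclusion. Sections 13.1.1 and 13.2.1 give opposite results for a subject stopped for pain, and 6.1, 8.2 and the interim rule do not settle whether he counts towards the 14.

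Under complete-case handling, the subjects lost would come mainly from the naloxone day: about 16% against 0.1% at SD 1, and up to 31% against 7% at SD 2. ΔSPID would fall by roughly 0.3 to 1.5 of the planned 5 units. These sizes rest on normal ratings, the planned means, an SD during infusion of 1 to 2, correlation 0.5 between components, a between-day correlation of 0 to 0.7, and baselines that cancel. The direction does not depend on the exact values within that range. With 18 treated at SD 1 the power loss is small (0.88 in the illustration, against the planned 0.90); with 14 treated it is not (0.73).

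**What to change.** - **13.2.1:** make the primary test the paired comparison of SPID between naloxone and placebo, using the 13.1.1 value at the last step reached on each day. If the infusion is stopped before the step assessment could be made, use the ratings taken at the stop. Keep the step-wise analysis as secondary, by a mixed model that retains subjects with missing steps.
- **8.2, 6.1 and 13.1.1:** state that subjects stopped for pain or given rescue are evaluable and count towards the 14 at the interim analysis.
- **12.4:** state that data collected before a code break stay in the analysis.

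The stopping rule itself is not touched. The cost is wording, plus recording the three pain ratings when an infusion is stopped. The downside is that ratings at a stop may be incomplete, since a subject in pain may not be able to do the chewing or pressure test. The text should therefore say what is used when only resting pain is recorded.

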### 8.3 Reasons to withdraw a participant from the study

A participant can be excluded from the study under the following conditions:

- If the participant wishes to withdraw from the trial
- Violation of the protocol rules

### 8.4 Procedures for participants withdrawing from the study

In accordance with the Declaration of Helsinki with appropriate amendments, the participants have the right to end their participation in the study at **any** time for **any** reason. The investigator has also the right to withdraw a participant from the study at **any** time. Reasons for a participant withdrawing before the end of the study will be recorded and documented in the participant’s Case Report Form.

